### Intervention

The beverage powders (fortified and unfortified) will be packaged in sealed plastic bags. Each participant in the intervention group will receive 1 pack of the baobab pulp-fortified pearl millet powder (60 g millet powder enriched with 9 g baobab pulp) daily. Similarly, each participant in the control group 1 will receive 1 pack of the unfortified pearl millet beverage powder (60 g millet powder) daily. Participants will prepare the beverage themselves by simply dissolving the powders in 300 ml of cold/chill water (sachet-treated water) and drink instantly in the presence of trained teachers and/or research assistants. As such, each participant will be provided with a cup, teaspoon and 300 ml cold/chill water for the preparation of the beverage. Participants will be fed the beverages once a day, five times a week (Monday to Friday) for six consecutive months (including school vacation time)^(38,52)^. Feeding will be done during the first break (10.00–10.30) and participants will be asked to report to the study team as soon as possible if they commence the intake of any Fe and folic acid supplements during the study period. Any leftover from each participant’s cup will be weighed using an electronic kitchen scale and the amount of beverage consumed computed as weight of beverage served minus weight of leftover.

In control group 2, participants will receive neither the baobab pulp-fortified pearl millet beverage nor the unfortified pearl millet beverage, but their usual Fe -folic acid tablets given by Ghana Health Service under the Girls’ Iron-Folate Tablet Supplementation Programme for the same duration, to allow for the efficacy of the fortified beverage to be evaluated in comparison with the standard Fe-folic acid supplementation regimen, as both treatments will provide roughly the same amount of Fe weekly. Hence, each participant in this group will receive 1 Fe-folic acid tablet (60 mgFe and 400 μg folic acid) once a week for six months. The girls will be given the tablets every Wednesday of the week after a lunch meal in the presence of teachers and/or research assistants^(72)^.

During school vacation time, the participants and their teacher will have to agree on a convenient time to come to school for the intake of the beverages or tablets^(38)^. For participants who fail to turn up during a feeding session, the teacher and/or field assistant will visit them to administer the beverage or tablets^(38)^.

Regarding criteria for discontinuing or modifying allocated interventions, the interventions will not be allowed to be modified and participants are required to consume all beverages/tablets provided in approved quantities, and can voluntarily withdraw at any time. Participants can also be permanently excluded for reasons such as refusal to partake in any required study procedures.

Also, all participants will be sensitised on the benefits of the interventions, as a crucial first step to improving compliance and continued participation (participant retention). The study team will also be available throughout the trial period to identify and address any barriers to compliance and continued participation. Participants will also be made to consume the beverages/tablets in the presence of the study team to ensure compliance.

### Mid-way treatment

All participants will also be re-treated against intestinal parasites at mid-way using a single dose of albendazole 400 mg chewable tablets. Participants will also be re-tested for malaria at midpoint. Those who test positive for malaria will be treated by the study physician.

### Post-intervention assessment

At the end of the feeding intervention, post-intervention assessment will be done immediately. Dietary intake, anthropometry and the biochemical indices will be reassessed.

### Outcome measures

The primary outcomes will be serum ferritin (ug/l) and Hb (g/dl) concentrations of participants. Secondary outcomes will be prevalence of Fe deficiency, Fe deficiency anaemia and BMI-for-age.

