### Baseline assessment

A pre-tested structured questionnaire will be employed to document information on participants’ socio-demographic characteristics and dietary consumption patterns. Participants’ anthropometric measurements will be taken to assess their nutritional status (online Supplementary file 3). Biochemical indices such as Hb concentration, serum ferritin and C-reactive protein of participants will also be assessed to diagnose Fe deficiency, Fe deficiency anaemia and anaemia. WHO (2020) currently recommends serum ferritin as an adequate marker of Fe status when assessed along with inflammation/infection markers (C-reactive protein and/or *α*-1 acid glycoprotein) and ferritin adjusted as necessary^(55)^.

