#### Haematological and biochemical assessment

At baseline and end-line, about 5 ml of non-fasting venous blood sample will be collected from each participant by a phlebotomist and analysed for Hb concentration, serum ferritin and C-reactive protein.

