##### Determination of serum ferritin and C-reactive protein

The whole blood will be put in the gel-coated serum separator vacutainers and preserved at 4°C in an ice chest containing cold packs while in the field. The serum will be separated by means of a centrifuge at 500 rpm for 5 min at refrigerated temperature. The separated serum will be aliquoted and frozen at −80°C. The serum will be transported to the testing laboratory on frozen ice packs in an ice chest, when time is due for analysis. The ELISA technique will be used to assess serum concentrations of ferritin and C-reactive proteins. Fe deficiency will be defined as serum ferritin concentrations < 15 ug/l for healthy individuals and < 70 ug/l for individuals with inflammation/ infections^(55)^ and inflammation/infection as C-reactive proteins > 5 mg/l^(69)^.

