### Statistical analysis

Data analysis will be done using Statistical Package for Social Sciences version 22 and WHO AnthroPlus software. Shapiro–Wilk and Kolmogorov–Smirnov tests will be done to test quantitative data for normality. Data that turns out not to be normally distributed will be analysed using non-parametric tests. Continuous data will be reported as means and sd, whilst categorical variables will be presented as frequencies and percentages. Data will be analysed using intention to treat analysis. One-way ANOVA will be used to compare means of serum ferritin and Hb levels among the three study groups (arms). Tukey’s post hoc test of one-way ANOVA will be performed to determine intergroup differences. Paired *t* test will be used to determine change in means of serum ferritin and Hb levels within groups (baseline and end-line). Relationship between covariates and outcome variables will be determined using multivariate linear and binary logistic regression analyses. WHO AnthroPlus software will be used to compute BMI-for-age Z-scores to determine participant’s nutritional status. Missing data will be resolved via multiple imputations. *P* < 0·05 will be considered significant at two-tailed tests.

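### The primary ferritin comparisons have no CRP term, although the protocol relies on inflammation-adjusted ferritin as its Fe marker and measures CRP at both visits

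*Protocol article*

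**What the plan says.** **Outcome.** Outcome measures: "The primary outcomes will be serum ferritin (ug/l) and Hb (g/dl) concentrations of participants". No inflammation-corrected version is named. Prevalence of Fe deficiency and of Fe deficiency anaemia are secondary.

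**Reason for using ferritin.** Baseline assessment cites WHO for ferritin as an adequate marker when assessed with CRP and/or another acute-phase protein, "and ferritin adjusted as necessary".

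**Collection of CRP.** Haematological and biochemical assessment: "At baseline and end-line, about 5 ml of non-fasting venous blood sample will be collected from each participant", for Hb, ferritin and CRP. Table 1 agrees.

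**Use of CRP.** The section on determining ferritin and CRP sets the Fe deficiency cut-off at 15 µg/l for healthy girls and at 70 µg/l "for individuals with inflammation/ infections", with inflammation defined as CRP above 5 mg/l. No other use of CRP in the analysis is stated.

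**Tests.** Statistical analysis: "One-way ANOVA will be used to compare means of serum ferritin and Hb levels among the three study groups (arms"), followed by Tukey's test. Within arms, a paired t "test will be used to determine change in means of serum ferritin and Hb levels within groups (baseline and end-line"). Non-parametric tests replace these if the data are not normal. A further sentence reads: "Relationship between covariates and outcome variables will be determined using multivariate linear and binary logistic regression analyses".

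**Design.** Randomisation assigns two schools to each arm. Malaria is tested at baseline and halfway, and positives are treated. All arms are dewormed before feeding and again at the midpoint.

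**The concern.** Ferritin rises with inflammation as well as with Fe stores. The protocol's own higher cut-off for inflamed girls presupposes this. The plan therefore recognises that inflammation changes what a ferritin value means, but carries this only into a binary secondary outcome and not into the continuous primary outcome from which that outcome is derived.

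Two comparisons are exposed:

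- **Between arms.** Infection tends to be shared within a school, and each arm has only two schools. An episode in one school around the end-line blood draw touches half an arm, and randomising six schools cannot be relied on to even this out.
- **Within arms.** If infection is more or less common at end-line than at baseline, the paired t test counts that shift as a change in Fe status.

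Malaria is not tested at end-line, so CRP is the only infection or inflammation marker taken when the end-line ferritin is measured. At stake is whether a ferritin difference, or its absence, can be read as an Fe result.

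**Working it through.** **1. The plan's own figures (Sample size section).** Inputs: SD 20.1 µg/l, effect 9.4 µg/l, z-values 1.96 and 0.84.

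- n = 2 × 20.1² × (1.96 + 0.84)² / 9.4² = 71.7, so 72 per arm, as stated.
- Design effect 1 + 0.0009 × 42 = 1.0378; 72 × 1.0378 = 74.7; × 1.15 = 85.9, so 86 per arm, as stated.

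The sample size is not the issue here. These figures only give the scale.

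**2. Where CRP enters.**

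| Analysis | CRP used? |
|---|---|
| ANOVA and Tukey on ferritin (primary, between arms) | No |
| Paired t test on ferritin (primary, within arms) | No |
| Fe deficiency (secondary) | Yes, through the cut-off |
| Covariate regression | Not named, and not tied to the arm comparison |

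**3. Size of a shift.** The documents give neither the share of girls with raised CRP nor the ferritin rise that goes with it, so both are assumed:

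shift = (gap between arms in the share with CRP > 5 mg/l) × (ferritin rise in inflamed girls)

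| Gap | Rise 20 µg/l | Rise 30 µg/l |
|---|---|---|
| 5 points | 1.0 (11% of 9.4) | 1.5 (16%) |
| 10 points | 2.0 (21%) | 3.0 (32%) |
| 20 points | 4.0 (43%) | 6.0 (64%) |

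Over a wider grid, gaps of 5-30 points and rises of 10-40 µg/l, the shift runs from 0.05 × 10 = 0.5 to 0.30 × 40 = 12 µg/l.

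**4. Is a 10-point gap plausible?** With 43 girls in each of two schools, a 20-point excess in one school gives 0.20 × 43/86 = 10 points for the arm. Alternatively, assume a mean share of 20% and a between-school SD of s. The SD of the gap between two arms is √[2 × (s²/2 + 0.2 × 0.8/86)], which is 7.9 points for s = 5 points and 11.7 points for s = 10 points. The between-school part of this SD equals s itself, 5-10 points. The rest is individual sampling variation, which the ferritin SD already covers.

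**5. Consequence, given such an imbalance.** Completers per arm: 86 × 0.85 ≈ 73. SE = 20.1 × √(2/73) = 3.33 µg/l. By normal approximation, ignoring clustering and Tukey's correction:

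| Shift | Two-sided false-positive rate | Power for 9.4 µg/l if the shift opposes it |
|---|---|---|
| 0 | 5% | 81% |
| 2 µg/l | 9% | 60% |
| 3 µg/l | 15% | 49% |

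**The case against.** **The regression sentence may cover CRP.** CRP is an obvious candidate covariate. But the sentence does not name it and concerns relationships between covariates and outcomes, while the arm comparison is assigned to ANOVA and Tukey. It leaves room for an adjusted analysis without committing to one.

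**A condensed article may leave the correction method elsewhere.** The exact formula could be left out. Here, though, the article names the outcome, the tests and one specific use of CRP, so a reader who follows it compares measured ferritin. The cut-off and the WHO statement cite the same reference, so the cut-off may be how the authors meant to adjust. That deals with prevalence and leaves the continuous primary untouched.

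**Deworming, malaria treatment and weekly physician checks reduce infection.** This stands in part. They apply in all arms and should narrow differences between schools. They do not measure or remove inflammation at end-line, and by lowering infection between visits they could themselves move ferritin within arms.

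**Keeping measured ferritin primary is defensible.** End-line CRP is post-randomisation, and a treatment that changed CRP would lose part of its effect under correction. This is a real cost and the reason to retain the unadjusted result.

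Three stronger readings are tempting and not supported:

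- *The protocol itself says that ferritin must be adjusted.* It reports a WHO recommendation, worded conditionally.
- *Inflammation raises ferritin by 55 µg/l, the gap between 15 and 70.* That is a distance between cut-offs, not a mean rise. A rise of 55 would by itself contribute variance p(1 − p) × 55² = p(1 − p) × 3025, where p is the inflamed share. This exceeds the planned total of 20.1² = 404 for any p between about 16% and 84%. A rise of 30 adds at most 0.25 × 900 = 225, which fits at any share.
- *The arm comparison is systematically biased.* Schools are randomised, so the between-arm problem is chance imbalance and extra between-school noise, in either direction. An ANOVA that ignores clustering is a separate matter and should not be counted again here.

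**Conclusion.** The point holds. The protocol accepts ferritin as an Fe marker on a condition that its primary ferritin tests, as written, do not meet, although the data to meet it are collected at both visits.

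The size is illustrative. With a 10-point gap in raised CRP and a 20-30 µg/l rise, both assumed, the arm difference moves by 2-3 µg/l, or 21-32% of the planned effect. That is less than one standard error (3.33 µg/l), so it would not usually decide the result alone. It is enough to raise the false-positive rate or cut power noticeably when it occurs. Smaller or larger inputs scale the figure in proportion. The direction is unknown in advance.

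The change should be made before the arms are compared. It would also remove a later choice between raw and adjusted ferritin.

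**What to change.** Amend Outcome measures and Statistical analysis as follows:

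- Define the primary ferritin outcome as log ferritin corrected for CRP. Estimate the slope of log ferritin on log CRP in baseline data pooled over all arms, so that treatment cannot influence it. Use it to correct baseline and end-line values to a low reference CRP fixed in advance.
- Use the corrected values in both the between-arm and the within-arm comparisons.
- Report unadjusted ferritin, and the subset with CRP of 5 mg/l or less, as sensitivity analyses.
- State that end-line CRP is post-randomisation, so both the correction and the subset condition on something treatment might affect. The unadjusted analysis shows whether this matters.
- Say whether CRP also belongs in the covariate regression and how that regression relates to the arm comparison.

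**Cost.** Analysis wording only, with no new samples, assays or visits. The slope can be estimated without knowledge of allocation, so the analyst's blinding is kept. Results on the log scale are ratios, so a back-transformed summary is needed beside the planned 9.4 µg/l. The correction does not cure the small number of schools. It removes only the part of the between-school noise that CRP captures.

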### Statistical analysis

Data analysis will be done using Statistical Package for Social Sciences version 22 and WHO AnthroPlus software. Shapiro–Wilk and Kolmogorov–Smirnov tests will be done to test quantitative data for normality. Data that turns out not to be normally distributed will be analysed using non-parametric tests. Continuous data will be reported as means and sd, whilst categorical variables will be presented as frequencies and percentages. Data will be analysed using intention to treat analysis. One-way ANOVA will be used to compare means of serum ferritin and Hb levels among the three study groups (arms). Tukey’s post hoc test of one-way ANOVA will be performed to determine intergroup differences. Paired *t* test will be used to determine change in means of serum ferritin and Hb levels within groups (baseline and end-line). Relationship between covariates and outcome variables will be determined using multivariate linear and binary logistic regression analyses. WHO AnthroPlus software will be used to compute BMI-for-age Z-scores to determine participant’s nutritional status. Missing data will be resolved via multiple imputations. *P* < 0·05 will be considered significant at two-tailed tests.

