### Sample size

The formula employed for the sample size estimation is: N = 2S

(

+

/

^(36)^

where N is sample size

sd is standard deviation; estimated to be 20·1 μg/l for serum ferritin^(37)^ and 1·2 g/dl for Hb (anaemia)^(32)^.

 = 1·96 (From Z table) at a precision of 5 % and CI of 95 %.

 = 0·84 (From Z table) at 80 % power.

d is effect size; estimated to be 9·4 μg/l for serum ferritin^(38)^ and 0·65 g/dl for Hb (anaemia)^(39)^.

Sample size (Serum ferritin): N = 2

(

*+*

*/*

= 72

Sample size (Hb): N = 2

(

*+*

*/*

= 53

The larger sample size (N = 72) of the 2 variables (serum ferritin and Hb) will be used for the study.

As a cluster randomised controlled trial, cluster design effect has to be considered in the sample size calculation to improve the power and precision of the study^(40,41)^. The required sample size for a cluster randomisation trial is obtained by multiplying the sample size of the individual randomisation trial (N = 72) by the design effect^(42,43)^. Design effect = 1 + intra-cluster correlation (m-1), where m is the average cluster size. An estimated intra-cluster correlation of 0·0009^(44)^ will be used. The average size of each cluster (school) in the study district is estimated to be 55 adolescent girls, with the number of anaemic adolescent girls in each school estimated to be 43^(32)^, thus m = 43. Design effect = 1 + 0·0009(43–1) = 1·037. Hence, considering the design effect of 1·037 and 15 % attrition rate, the sample size will be 86 participants per arm (258 participants for the 3 arms, with 43 participants to be chosen from each school).

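### A normality pre-test decides how the primary ferritin outcome is analysed, and its rank-test fallback would not estimate the effect the trial was sized on

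*Protocol article*

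**What the plan says.** Outcome measures fixes the scale of both primary outcomes: "The primary outcomes will be serum ferritin (ug/l) and Hb (g/dl) concentrations of participants". Sample size works from a ferritin SD of 20.1 µg/l and a difference in means of 9.4 µg/l. Ferritin needs more girls than haemoglobin, so it sets the size: "The larger sample size (N = 72) of the 2 variables (serum ferritin and Hb) will be used for the study".

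Statistical analysis names one-way ANOVA with Tukey comparisons between arms and paired t tests within arms, both on means. It makes them conditional: "Shapiro–Wilk and Kolmogorov–Smirnov tests will be done to test quantitative data for normality", and then "Data that turns out not to be normally distributed will be analysed using non-parametric tests". No transformation is mentioned. Nothing says which normality test governs if they differ, or whether they apply by arm, pooled, at baseline or at end-line. The same section says "Continuous data will be reported as means and sd, whilst categorical variables will be presented as frequencies and percentages", with no exception for skewed variables. Regression is also planned, but for another purpose: "Relationship between covariates and outcome variables will be determined using multivariate linear and binary logistic regression analyses".

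The introduction ends with two hypotheses. The fortified beverage should do better than the unfortified one, and it should do about as well as, or better than, routine iron-folate.

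**The concern.** The analysis of a primary outcome should be known before the data are seen. Here it depends on the result of a preliminary test, and the two branches answer different questions. ANOVA with Tukey comparisons estimates differences in mean ferritin in µg/l. A standard rank test asks whether values in one arm tend to be higher than in another, and usually reports only a p-value.

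The effect estimate is what is at stake. The trial was sized on a mean difference that the rank branch does not estimate. The iron-folate hypothesis needs an estimate with an interval, because a non-significant rank test does not show that two treatments are similar. The planned multiple imputation also sits awkwardly with rank tests, since the usual pooling rules need an estimate and a variance from each imputed data set.

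**Working it through.** **1. The plan's own figures.** Inputs from Sample size: SD 20.1 and difference 9.4 µg/l for ferritin; z values 1.96 and 0.84; intra-cluster correlation 0.0009; 43 girls per school; 15% attrition.

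- Ferritin: 2 × (20.1 × 2.80 / 9.4)² = 71.7, so 72 per arm, as stated.
- Design effect: 1 + 0.0009 × 42 = 1.0378.
- 72 × 1.0378 = 74.7; × 1.15 = 85.9, so 86 per arm, as stated.

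The trial's size therefore rests on comparing means in µg/l.

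**2. How likely is the switch?** The article gives neither the mean nor the shape of ferritin, so both are assumed here: log-normal, SD 20.1, control mean 15 to 60 µg/l. The number per arm at end-line is 86 × 0.85 = 73. Values come from 2,000 simulated trials per row with independent girls. Power is for one pairwise comparison at two-sided 0.05, with a shift on the log scale that raises the mean by 9.4 µg/l. The second column is Φ(−mean / 20.1), the share of a normal curve that would fall below zero.

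| Assumed mean | Normal curve below 0 | Shapiro–Wilk rejects, one arm | Power: t test, raw | Power: rank test | Power: t test, log | Ratio (mean + 9.4) / mean |
|---|---|---|---|---|---|---|
| 15 | 22.8% | 100% | 0.63 | 0.80 | 0.82 | 1.63 |
| 20 | 16.0% | 100% | 0.66 | 0.78 | 0.80 | 1.47 |
| 25 | 10.7% | 99.9% | 0.67 | 0.76 | 0.78 | 1.38 |
| 30 | 6.8% | 99.9% | 0.71 | 0.76 | 0.78 | 1.31 |
| 40 | 2.3% | 98% | 0.72 | 0.75 | 0.76 | 1.24 |
| 60 | 0.1% | 82% | 0.75 | 0.75 | 0.77 | 1.16 |

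Applied to the pooled arms, Shapiro–Wilk rejects in about 100% of runs throughout. Ferritin cannot be negative, so at low means an SD of 20.1 is hard to square with a normal shape. At 40 or above that argument has little force.

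**3. Can the two tests disagree?** Under the same assumptions (600 runs, arms of 73), Shapiro–Wilk and the Lilliefors-corrected Kolmogorov–Smirnov test disagree in 0–6% of arms at means of 20–30, 21% at 40, 33% at 50 and 38% at 60. The rule is least clear where the switch is least certain.

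**4. Does the rule inflate type I error?** Simulated with three independent arms of 73, Shapiro–Wilk rejection in any arm leading to Kruskal–Wallis, and 5,000 runs per setting: 4.8% to 5.1% for log-normal data at means of 20 to 100 µg/l, and 5.2% to 5.5% for normal data. Simulation error is about √(0.05 × 0.95 / 5000) = 0.3 percentage points. There is no material inflation. This check leaves out Kolmogorov–Smirnov and clustering.

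**5. Does ignoring school hurt one branch more?** With two schools per arm, 37 girls each and 4,000 runs, type I error for Kruskal–Wallis against ANOVA on logs is 6.0% v 5.9% at an intra-cluster correlation of 0.0009, 11.1% v 11.0% at 0.01, and 32.9% v 34.0% at 0.05. Both branches suffer alike.

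**6. What would a fixed model give?** Take log ferritin adjusted for baseline log ferritin, assume a baseline to end-line correlation of 0.6 (not in the article), 73 per arm and no clustering. Power is then about 0.90 to 0.93 at means of 20 to 60 µg/l (4,000 runs). In the same runs the unadjusted log-scale t test has 0.76 to 0.79 and the rank test 0.73 to 0.77. Most of the gain comes from the baseline value, not from the logarithm.

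**The case against.** Several stronger readings are tempting, and the documents do not support them.

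- *The switch costs power.* It does not. Under skewed ferritin the rank test has power of 0.75 to 0.80, against 0.63 to 0.75 for the raw t test, so it is as good or better.
- *A data-driven choice of test breaks error control.* The check in step 4 shows no material inflation. If the pre-test nearly always rejects, the choice is in effect fixed anyway.
- *The rank branch throws away adjustment for baseline and school.* The planned ANOVA and paired t tests contain neither term, and the regression is not described as the comparison of arms. Their absence is a separate weakness of both branches.
- *Ferritin will certainly be skewed.* The article does not say so and gives no mean. It also uses a deficiency cut-off of 70 µg/l under inflammation, so a mean well above 15 is possible.
- *No result in µg/l is possible.* A Hodges–Lehmann shift is in µg/l, and means and SDs would still be tabulated. But no such shift is planned, and the tabulated means would not match the test.
- *Haemoglobin is affected too.* Nothing shows this.

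It is also fair to say that the names of the fallback tests may be left to an analysis plan that is not shown, that the analyst is blinded to allocation, and that a log model is one sound choice among several which itself moves away from a difference in µg/l. All of that stands. None of it answers the narrower point: the article itself states a rule under which the quantity estimated for a primary outcome is unknown until the data arrive.

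**Conclusion.** The point holds in limited form. A normality pre-test determines the analysis, and so the estimand, of the outcome that set the sample size. If ferritin is log-normal with SD 20.1 µg/l, the planned comparison of means would be replaced in 82% to 100% of cases judged on a single arm, and almost always if judged on the pooled data. Shape and mean are assumptions, and the switch becomes less certain as the mean rises. The loss is one of interpretation: no estimate of the 9.4 µg/l difference, and no interval with which to judge the fortified beverage against iron-folate. This is a cheap improvement worth making before analysis, not a flaw that invalidates the trial.

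**What to change.** - Delete the normality-test rule for the two primary outcomes.
- State that end-line log ferritin will be compared between arms in a linear model adjusted for baseline log ferritin, with geometric mean ratios and 95% confidence intervals.
- Analyse haemoglobin untransformed, adjusted for its baseline value.
- Summarise ferritin by geometric mean or median in place of mean and SD.
- Keep a rank test as a sensitivity analysis only.
- Handle any school term consistently with the separate clustering question. With only two schools per arm it cannot simply be added to the model.

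**Cost.** No new data are needed, since both baseline values are already collected. The text must change, and it brings in a baseline-adjusted model that is not planned at present. The ferritin effect becomes a ratio, so its back-translation should be given against the 9.4 µg/l benchmark. That benchmark corresponds to a ratio of 1.47 at a control mean of 20 µg/l but 1.16 at 60, so the control-arm level used must be stated.

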## Methods

### Study design

The study will be a three-arm parallel cluster randomised controlled trial. Participants in arm 1 (Intervention group) will receive pearl millet beverage enriched with baobab pulp, while participants in arm 2 (Control group 1) will receive unfortified pearl millet beverage, once a day, five times a week, for six months. Participants in arm 3 (Control group 2) will receive weekly Fe -folate supplementation also for six months. The study outcomes will be assessed twice, at baseline and end-line.

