### Randomisation

An independent statistician will randomly assign the selected schools (clusters) to the 3 arms of study at a ratio of 1:1:1 (2 schools per arm) using the formula =RAND() in Microsoft Office Excel Software. Participants will be informed of their intervention allocation after baseline data collection is completed. This cluster randomisation method will prevent cross-contamination among the study arms through beverage sharing among participants^(35)^. Due to the nature of the intervention, blinding of participants and study team will not be possible; however, the data analyst will be blinded to the allocation of the participants.

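### Six schools are randomised, two per arm, but the between-arm tests named for ferritin and Hb treat girls as independent, so their validity rests on one borrowed ICC

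*Protocol article*

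**What the plan says.** The Study design section states: "The study will be a three-arm parallel cluster randomised controlled trial". Under Randomisation, the allocation step is to "randomly assign the selected schools (clusters) to the 3 arms of study at a ratio of 1:1:1 (2 schools per arm"). The Sample size section says that "cluster design effect has to be considered in the sample size calculation" and applies a design effect of 1.037, from an ICC of 0.0009 taken from a cited source and 43 girls per school.

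Under Outcome measures, "The primary outcomes will be serum ferritin (ug/l) and Hb (g/dl) concentrations of participants". The Statistical analysis section gives two between-arm procedures for these outcomes: "One-way ANOVA will be used to compare means of serum ferritin and Hb levels among the three study groups (arms") and "Tukey’s post hoc test of one-way ANOVA will be performed to determine intergroup differences". It adds paired t tests within each arm, and regressions described as follows: "Relationship between covariates and outcome variables will be determined using multivariate linear and binary logistic regression analyses". Neither this section nor any other mentions a school term, a mixed model, a cluster-robust variance or a school-level summary.

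**The concern.** The design and sample size treat the school as the unit, while the named tests treat the girl as the unit. One-way ANOVA and Tukey judge the arm differences against the spread between girls. In a cluster trial they should be judged against the spread between schools in the same arm. Each arm has two schools, so one unusual school moves half an arm. School differences are plausible on the protocol's own account: it lists malaria, intestinal worms and diet among the determinants of anaemia in Ghana, draws each school from a different community, and has teachers help to supervise intake.

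At stake is whether a significant result for a primary outcome can be credited to the beverage rather than to the schools that happened to receive it. Inflating the sample size by a design effect does not repair a test that ignores clustering.

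**Working it through.** **1. The protocol's sample size.** Inputs from the Sample size section: SD 20.1 and difference 9.4 μg/l, z values 1.96 and 0.84, ICC 0.0009, m = 43, attrition 15%.
- Per arm before clustering: 2 × (20.1 × 2.80 / 9.4)² = 71.7, so 72.
- Design effect: 1 + 0.0009 × 42 = 1.0378 (stated as 1.037).
- 72 × 1.0378 = 74.7, and 74.7 × 1.15 = 85.9, so 86 per arm.

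The stated 86 is reproduced. The calculation allows for the ICC but uses normal quantiles, so it takes no account of how few schools there are.

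**2. Degrees of freedom.** The plan is intention to treat with multiple imputation, so all 258 girls count: 258 − 3 = 255 residual df. Between schools there are 6 − 3 = 3. The two-sided 5% critical t is 1.97 on 255 df and 3.18 on 3 df.

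**3. Type I error of the planned F test.** With m girls per school, the variance of an arm mean is larger by the design effect 1 + (m − 1) × ICC than ANOVA assumes. The standard error is therefore understated by about its square root. Null trials were simulated with 3 arms, 2 schools per arm and normal data with a school effect. The value m = 37 reflects 15% attrition (43 × 0.85 = 36.6). Only ICC 0.0009 comes from the protocol; the other values are assumptions, shown as a range.

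| ICC | SE understated by factor (m = 37) | Type I error, m = 37 | Type I error, m = 43 |
|---|---|---|---|
| 0.0009 | 1.02 | 5.5% | 5.6% |
| 0.01 | 1.17 | 11% | 12% |
| 0.02 | 1.31 | 18% | 20% |
| 0.05 | 1.67 | 35% | 39% |
| 0.10 | 2.15 | 54% | 57% |

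Tukey's chance of at least one false pairwise difference is almost the same as the F test's in each row. An F test on the six school means (2 and 3 df) held 5% at every ICC.

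**4. Power of the valid analysis.** The standardised difference is 9.4 / 20.1 = 0.468. For two schools per arm, the standard error of a difference in SD units is √[2 × (ICC + (1 − ICC)/37) / 2]. On 3 df the critical value is 3.18 unadjusted. With Tukey for three pairs it is 5.91 / √2 = 4.18. Power comes from the non-central t distribution.

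| ICC | Standard error | Non-centrality | Power, unadjusted | Power, Tukey |
|---|---|---|---|---|
| 0.0009 | 0.167 | 2.80 | 48% | 30% |
| 0.01 | 0.192 | 2.44 | 39% | 24% |
| 0.05 | 0.275 | 1.70 | 23% | 13% |

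These figures ignore any gain from baseline adjustment. Most of the loss comes from the 3 df: even at an ICC of zero, unadjusted power is 49%.

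**The case against.** The strongest defence is that, on the only ICC the protocol gives, the planned tests are nearly right: the standard error is about 2% too small and type I error is about 5.5%. That stands. A reader might infer from the table that the trial's error rate is 11% or more. The document does not support that, because those rows rest on assumed ICCs. What remains is that the planned test is sound only if one borrowed value holds, and the analysis has no protection if it does not.

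A second defence is that an article leaves detail to an analysis plan. It carries little weight here, because the tests are named outright and conflict with the stated design.

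Three further inferences should not be drawn.
- The paired t tests are not shown to be in error to the same degree. They are within-arm tests, and clustering affects them through the ICC of the change, which is not given.
- The article's silence on reporting an ICC does not show that none will be estimated. Nor could an estimate confirm 0.0009: with six schools of 37 girls and a true ICC of 0.0009, the ANOVA estimate runs from about −0.03 to +0.06 (central 95% of simulations) and is zero or below about 59% of the time.
- The section promises no confidence intervals and labels no single test as primary. The point is about the P values of the only between-arm tests named for the primary outcomes.

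**Conclusion.** The point holds as a conflict between the stated design and the stated analysis, and the analysis text should be changed. The size of the harm depends on the ICC: negligible at 0.0009, about a doubling of the error rate at 0.01, and roughly sevenfold at 0.05. The calculations assume normal outcomes, equal school sizes and 37 girls per school after attrition. The conclusion that only 3 degrees of freedom inform the arm comparison needs none of these assumptions; it follows from six schools and three arms. The larger consequence is for power. A valid analysis of two schools per arm does not reach the stated 80%, even if the protocol's ICC is exactly right.

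**What to change.** Replace the ANOVA and Tukey sentences with an analysis of the six school means:
- Adjust each girl's end-line value for her baseline value in a first stage that leaves out arm, then average by school. This keeps 3 df for the arm comparison.
- Compare arms on 3 df, and keep Tukey on those 3 df for the three pairwise contrasts, so that the multiplicity control already planned is not lost.
- Accept a mixed model with a random school intercept only if its contrasts are forced to between-school df. With six schools the estimated school variance will often be zero, and default software would then return to girl-level inference.
- Use school-level summaries for Fe deficiency and Fe deficiency anaemia, and include school in the imputation model.
- State that the paired t tests describe change within an arm and carry no between-arm conclusion.
- Report the observed ICCs for information, not as a check on 0.0009.

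The non-parametric fallback has the same fault if it is run on individual girls. On six schools it is very limited: there are 6!/(2!·2!·2!) = 90 allocations, which form 15 distinct groupings for an overall test, so the smallest possible P value is 1/15 = 0.067. Transforming a skewed outcome before averaging is the more practical route.

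The change needs no new data, but it is more than a wording edit. The Sample size section should replace 80% with the power of the valid analysis: about 48% unadjusted or 30% with Tukey at ICC 0.0009, and 39% or 24% at 0.01, before any gain from baseline adjustment. If schools can still be added, that is the effective remedy. If not, the between-arm conclusions should be worded to match the power available.
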